### Sample size estimation

The sample size was derived from pre-existing research using G Power v.3.1, considering significance level (*α*) = 0.05, power (1 − β) = 0.95, and given that the minimal clinically significant difference in patient’s hand function improvement, as per prior study data, is 9 points in the FMA-UE with an effect size of *d* = 1.13 [14]. Estimation via G Power software yielded a requirement of 44 samples. Considering potential subject attrition or termination, the sample size could be augmented by 10–15%, resulting in the adjusted sample size of *N* = 50, or 25 patients in each group. Consequently, the total sample size for both groups was formulated as 50.

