### Participants

Fifty eligible patients with upper limb motor dysfunction in stroke will be recruited from the outpatient and inpatient departments of the Department of Rehabilitation Medicine, Department of Neurology, and Department of Neurosurgery of the Second Hospital of Chongqing Medical University. Eligible patients had to satisfy the inclusion, exclusion criteria, and termination criteria (Table 1). Information about this trial will be posted via posters in the waiting area of the Rehabilitation Department and the Rehabilitation Medicine Clinic so that interested patients can contact the program director through their therapist. If an applicant meets the study criteria, then they will be invited to participate

**Table 1 Tab1:** Inclusion, exclusion criteria and termination criteria

**Inclusion criteria** 1. Meet the diagnostic criteria for stroke (including cerebral hemorrhage and cerebral infarction) formulated by the 4th National Cerebrovascular Disease Conference in 1995and confirmed by head CT or MRI, and the course of the stroke is 1 to 6 months 2. Abnormal hand function after stroke, Brunnstrom stage I-III, upper limb FMA-UE score lower than 47 3. The contralateral hand is in good condition 4. The age of the patient is 20-80 years old, and the gender is not limited 5. No progressive stroke performance, stable vital signs 6. Cognitive function is relatively intact, MMSE>17 or MoCA>24 7. Be able to follow the clinical treatment plan and sign the subject's informed consent
**Exclusion criteria** 1. Subjects with upper limb dysfunction before stroke 2. Subjects with visual impairment or unilateral neglect 3. Severe cognitive impairment or poststroke depression 4. Metal implants in the body, such as cardiac pacemakers and other metal devices 5. Suffering from serious underlying diseases, such as heart function level 4 (NYHA) or severe COPD 6. Subjects participating in other clinical trials at the same time 7. Subjects judged to be unsuitable for this trial, and withdrawing voluntarily 8. Subjects unable to undergo MRI scans
**Termination criteria** 1. Subjects have serious adverse events or adverse reactions 2. Subjects have other changes in their condition and cannot continue the trial 3. Subjects have significant problems in the design of the protocol or the trial and are unable to determine the efficacy

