#### Secondary outcomes

Brunnstrom is a motor function and muscle spasticity assessment method for the affected upper extremity [31]. It includes six stages: Grade 1: absence of random movement, no upper or lower extremity movement; Grade 2: joint response, comovement, and minimal random movements; Grade 3: random comovement with the ability to grasp but not extend; Grade 4: separation of movement, including the ability to pinch and make minor extensions; Grade 5: gradual restoration of muscle tone with fine movements, simultaneous yet independent extension of fingers; and Grade 6: motor ability approaching normalcy but speed and accuracy are suboptimal.

The Modified Barthel Index (MBI) assesses the mobility of stroke patients concerning their ability to carry out specific activities of daily living. These activities include eating, bathing, dressing, bowel and urinary control, toileting, bed and chair transfer, level walking, and stair walking [32, 33]. A total score of 100 can be achieved, and scores of 60 or higher indicate self-sufficiency. Independence positively correlates with the score.

We commonly use the Action Research Arm Test (ARAT) to assess the ability of the affected upper extremity and hand to handle objects of different sizes, weights, and shapes. The test assesses 19 tests of arm motor function, both distal and proximal. Each test is given a score of 0, 1, 2, or 3, with higher scores resulting in better function. The total ARAT score is the sum of the 19 tests, resulting in a maximum score of 57 [34]. Nine Hole Peg Test (9HPT): assesses the patient’s whole hand dexterity. The assessment requires the patient to take nine pegs from the container and insert them into a small pegboard, then remove and place them back into the container. The patient’s score depends on the speed of insertion and removal, with the faster the time, the higher the score [35].

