### Statistical analysis

Data management and analysis will be conducted in SPSS version 23. Groups will be compared at baseline using the *t* test for independent samples for the continuous variables, and the chi-square test for categorical data. The differences of the outcomes, including the FMA-UE, MBI, ARAT, and the 9HPT, between the groups at each of the trial time points will be analyzed using mixed-design 2-way repeated-measures analysis of variance (ANOVA), taking time (4 levels: preintervention, after 2 weeks, after 4 weeks of intervention and 3 months at the end of the trial for follow-up) as the within-subject factor and group (2 levels: TBMT and CG) as the between-subject factor. If participants drop out during the intervention period, they will not be excluded due to the principle of intention to treat (ITT). Furthermore, in instances of missing data, the continuation of observations (LOCF) method will be employed, whereby the last recorded observation preceding the gap in data will serve as a substitute. Unfavorable stroke outcomes correspond to lower FA values for corticospinal tracts, while robust functional recovery denotes elevated FA values. Subgroup analyses of FA values will be conducted based on the interquartile spacing (< 25% interval; 25–75% interval; > 75% interval) method post the inclusion of all individuals to standardize the baseline conditions of the patients. We will use linear regression model outcomes at 4 weeks post-treatment cessation as the dependent variable (FMA-UE). This model will include treatment assignment (TBMT vs. CT) and baseline outcome measure as fixed-effects, as well as patient characteristics (low or high impairment severity at baseline). We will examine differential impacts by fitting separate models with treatment-impairment severity. We will report relevant point estimates and standard errors for these models and conduct 5% level tests for interaction terms with two-sided alternative hypotheses. A *p*-value < 0.05 is deemed a statistically significant discrepancy.

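### Carrying the last score forward biases the FMA-UE difference in patients expected to improve, and may take power below the planned 95%

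*Protocol article*

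**What the plan says.** All references are to the protocol article.

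- **Statistical analysis.** Dropouts stay in the analysis under intention to treat. Gaps are handled thus: "the continuation of observations (LOCF) method will be employed, whereby the last recorded observation preceding the gap in data will serve as a substitute". The rule covers all missing data. The filled scores enter a two-way repeated-measures ANOVA with four time levels: before treatment, week 2, week 4 and 3 months.
- **Outcome measurements.** This section lists three assessments only: baseline, week 4 and week 12. It has no week-2 visit.
- **Abstract, Methods and analysis.** The primary outcome is mean change from baseline to week 4 and to the 12-week follow-up.
- **Sample size estimation.** The inputs are "considering significance level (*α*) = 0.05" and "power (1 − β) = 0.95", and the difference sought "is 9 points in the FMA-UE with an effect size of *d* = 1.13". This gives 44 patients. "Considering potential subject attrition or termination", the number is raised by 10–15% to 50, or 25 per arm.
- **Participants, Table 1.** Time since stroke at entry is 1 to 6 months.

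**The concern.** LOCF assumes that a patient stops changing on the day of the last assessment. That is a poor assumption here. The entry window and the change-from-baseline outcome both imply that scores should rise in both arms, and the trial is powered on a 9-point improvement. A patient lost before week 4 is then given part of the expected gain, or none if only the baseline score exists.

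The attrition allowance is meant to leave 44 real observations. The analysis rule instead puts 50 values into the ANOVA, some of them attenuated and all treated as measured. At stake are the size of the primary treatment difference, its power and, if the arms lose patients at different rates, the type I error. Unequal loss is plausible: patients learn their arm when the envelope is opened, and adverse reactions are a ground for termination.

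The two visit schedules decide how large the problem is. Without a week-2 visit, everyone lost during treatment carries baseline to week 4, which is exactly zero change. With one, patients lost after it carry a partial gain.

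**Working it through.** **Inputs from the article.** δ = 9 points, d = 1.13, α = 0.05, power 0.95, 25 per arm, allowance 10–15%. The sample-size section does not state sidedness. Two-sided is assumed because the article plans to "conduct 5% level tests for interaction terms with two-sided alternative hypotheses" and because it reproduces the stated number.

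**Assumptions not in the article.** g is the control-arm gain by week 4, taken as 0 to 8 points. f is the fraction of the gain that a dropout has shown at the last visit: 0 means baseline is carried, 0.5 means half the gain at week 2. p_T and p_C are the dropout proportions. The implied SD, 9 / 1.13 = 7.96, is taken as the SD of change. Dropout is unrelated to the score.

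**Step 1. The plan's own figure.** A two-sided two-sample t-test with d = 1.13 has 95.6% power at 22 per arm, so 44 is reproduced. (At 21 per arm it is 94.7%.) With 12% loss, 44 / 0.88 = 50. With all 25 per arm observed, power is 97.5%. The sample size is not in error.

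**Step 2. Expected difference under LOCF.**

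E = δ − (1 − f) × [p_T (g + δ) − p_C g]

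With equal dropout p this reduces to δ × [1 − p(1 − f)], whatever g is.

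- p = 12%, f = 0: 9 × 0.88 = 7.92
- p = 12%, f = 0.5: 9 × 0.94 = 8.46
- p = 10% to 15%, f = 0: 8.10 to 7.65
- p = 10% to 15%, f = 0.5: 8.55 to 8.33

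Unequal dropout, f = 0, g = 8:

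- 20% TBMT, 4% control: 9 − (0.20 × 17 − 0.04 × 8) = 9 − 3.08 = 5.92
- 4% TBMT, 20% control: 9 − (0.04 × 17 − 0.20 × 8) = 9 + 0.92 = 9.92
- No true effect, 20% against 4%: −(0.20 × 8 − 0.04 × 8) = −1.28

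**Step 3. Power and type I error.** These come from simulated trials with 25 per arm and random dropout, using a two-sample t-test on week-4 change as a simple stand-in for the planned ANOVA.

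| Dropout (TBMT / control) | f | g | Difference | Power |
|---|---|---|---|---|
| 12% / 12% | 0 | 0 | 7.92 | 94.6% |
| 12% / 12% | 0 | 4 | 7.92 | about 92–93% |
| 12% / 12% | 0 | 8 | 7.92 | 88.5% |
| 12% / 12% | 0.5 | 8 | 8.46 | about 96% |
| 20% / 4% | 0 | 0 | 7.20 | about 89% |
| 20% / 4% | 0 | 4 | 6.56 | about 78% |
| 20% / 4% | 0 | 8 | 5.92 | about 63% |
| 20% / 4% | 0.5 | 8 | 7.46 | about 90% |
| 4% / 20% | 0 | 8 | 9.92 | about 99% |

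With no true effect, g = 8 and 20% against 4% dropout, the nominal 5% test rejects in about 9% of trials if baseline is carried, and in just under 6% if half the gain is carried.

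**Step 4. Comparison without LOCF.** If missing scores are not carried forward and are missing at random, the expected difference stays at 9. Taking completers as an approximation, power is 95.9% at 10% loss (45 patients), 95.6% at 12% (44) and 94.7–95.1% at 15% (42–43).

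**The case against.** The strongest reply is about size. Within the planned allowance and with equal dropout, the bias is roughly 0.5 to 1.4 points of 9 and runs toward no effect. If half the gain is carried, power stays at about 96%. Even with baseline carried, losing exactly three patients per arm rather than 12% at random gives about 92% at an 8-point control gain. The control gain and dropout split are not in the article. All of this stands.

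A reader might go further in four ways that the documents do not support.

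- **That LOCF destroys the planned power.** It does not in general. Large losses need dropout concentrated in the TBMT arm, and the opposite imbalance raises nominal power while inflating the estimate.
- **That the bias vanishes only with equal dropout and no treatment effect.** By the formula it is zero whenever p_T (g + δ) = p_C g. With g = 8, 8% TBMT loss against 17% control loss gives 0.08 × 17 = 0.17 × 8 = 1.36, and the estimate is 9.0. The direction cannot be known in advance, but cancellation is possible.
- **That the 9HPT shows a further LOCF failure.** Enrolled patients are at Brunnstrom stages I–III, and grade 3 is described as "random comovement with the ability to grasp but not extend", so some may be unable to do the peg test at baseline. How inability is scored is a separate matter that an article may leave to the fuller documents. The article gives no stage mix and nowhere says that such patients are left out.
- **That exclusion 7 breaks intention to treat.** "Subjects judged to be unsuitable for this trial, and withdrawing voluntarily" stands under exclusion criteria, apart from the termination criteria, and can mean declining before enrolment. The analysis section expressly keeps dropouts. The wording is ambiguous at most.

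Sensitivity analyses may also sit in a plan that is not shown. That does not answer the point, because the main rule itself is stated and is LOCF.

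**Conclusion.** The concern holds in a bounded form. As written, the plan biases the primary FMA-UE difference whenever patients who would have improved are lost, and it may take power below 95%. At 12% equal dropout, 9 points becomes about 7.9 with baseline carried (power about 89% to 94–95% for a control gain of 8 to 0 points), or about 8.5 with half the gain carried (power about 96%). With unequal dropout the bias can favour either arm: about 5.9 or 9.9 points in the two 20%-against-4% cases, and about 9% type I error with no true effect, all at an assumed 8-point control gain with baseline carried.

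The mechanism rests on expected improvement, which is a sound inference from the entry window and the outcome but is not stated. The power and error figures also rest on the assumed gain, dropout split and carried fraction. Which carried fraction applies cannot be settled until the Outcome measurements and Statistical analysis sections agree on a week-2 visit.

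**What to change.** 1. Remove LOCF and replace the repeated-measures ANOVA with a likelihood-based mixed model on all observed scores of all randomised patients: baseline score as covariate, group, visit and group-by-visit, with unstructured covariance. SPSS, already named, fits this with MIXED. The model is valid under missing at random. The week-4 group contrast then estimates the difference that the sample size was built on.
2. Add one multiple-imputation sensitivity analysis that shifts the imputed scores of dropouts. It also brings in patients with no score after baseline, who contribute nothing to the model in item 1.
3. Reconcile the visit schedule. Either add the week-2 assessment to Outcome measurements or remove that level from Statistical analysis, so that the visit factor is defined.

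No extra patients are needed, and no extra visits unless the team decides to keep week 2. The cost is revised analysis wording and slightly more programming. The change should be made before unblinding.

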## Abstract

**Background and purpose:**

Research to date has lacked definitive evidence to determine whether mirror therapy promotes the recovery of upper extremity function after stroke. Considering that previous studies did not stratify patients based on structural retention, this may be one of the reasons for the negative results obtained in many trials. The goal evaluates the efficacy of TBMT (utilizing an innovatively designed mirror) versus standard occupational therapy for stroke patient’s upper limb functionality.

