**Fig. 1 Fig1:**
[figure not shown]
Conventional mirror therapy

The corticospinal tract (CST) is the primary descending motor pathway that connects cortical motor regions with spinal cord neurons, and it plays a crucial role in human upper limb mobility. Consequently, maintaining the structural integrity of the CST is crucial for determining the upper limits of upper limb recovery in patients. Studies have shown that the extent of CST injury is the optimal biomarker for successful rehabilitation of the upper extremity after stroke [17]. Baseline anatomical integrity assessment is essential to ensure patient balance and uniformity. Furthermore, this approach can predict functional recovery in chronic stroke for more effective neurological rehab treatment. Because there is a significant correlation between functional recovery and the preserved structural basis of the lesion [18]. Diffusion tensor imaging (DTI) is an MRI imaging technique that can detect lesions and display nerve fiber bundles in three dimensions [19]. Previous research has established that extracting CST bundle FA values from DTI data can yield valuable insight into their integrity and provide useful information about individualized rehabilitative strategies in stroke patients [20]. For this study, in an attempt to ensure the consistency of treatment efficacy irrespective of patient disease characteristics, we will employ DTI to assess the severity of CST degeneration in our subject patients. Post-enrollment, we will conduct a subgroup analysis to ensure balanced rehabilitation potential across various patient populations.

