## Methods/design

### Study design

This is a single-center, prospective, single-blinding, randomized controlled superiority trial. The objective will be used to evaluate the effectiveness of TBMT (using a newly designed mirror) compared to conventional occupational therapy on upper extremity functions of stroke patients. Patients will be randomly allocated in a 1:1 ratio into a control (*N* = 25) or TBMT group (*N* = 25), with the control group receiving conventional occupational therapy intervention and TBMT group receiving task-based mirror therapy in addition to CG. A professional team will measure relevant outcomes at baseline and 4 weeks after treatment.

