### Randomization and blinding

A total of 50 patients who meet the inclusion criteria will be randomly assigned to either the task-based mirror group or the control group. The randomization sequence will be generated by an independent statistician using SPSS Version 19.0. Patients will be assigned randomization numbers based on the order of enrollment. To maintain blinding, opaque sealed envelopes will be utilized to conceal group assignments. Patients will only become aware of their group after opening the envelope, which will be securely stored in a separate cabinet. Blinding of evaluators will be employed in this study to avoid bias stemming from subjective factors. The same investigator, who will be blinded to the treatment assignment, performed all the assessments. Additionally, statisticians will conceal the groupings and their significance, and the code will remain undisclosed until the analysis is finalized. In case of a severe incident during a trial, blinding may need to be undone for proper treatment. This decision must be endorsed by the trial’s lead researcher/medic, and recorded in the protocol, with utmost consideration given to minimizing bias and ensuring data quality.

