### Image data acquisition and preprocessing

For fiber tract identification, we will use automated fiber quantification (AFQ) software to identify 20 WM tracts in each participant’s brain [37]. The identification procedure included three primary steps: (1) whole-brain deterministic fiber tractography, (2) waypoint ROl-based tract segmentation, and (3) probability map-based fiber refinement. Twenty fiber tracts will be identified according to the predefined ROls and probability maps: bilateral thalamic radiation CST, cingulum cingulate, cingulum hippocampus callosum forceps major, callosum forceps minor, bilateral inferior front-occipital fasciculus (IFOF), bilateral inferior longitudinal fasciculus(lLF), superior longitudinal fasciculus (SLF), bilateral uncinate, bilateral arcuate. Then, each fiber bundle will be divided into 100 segments. Finally, the FA, MD, AD, and RD of each segment of each fiber bundle will be calculated. The automated calculation will be performed by MATLAB 2011b. First, the effective self-diffusion tensor will be computed from the movement and distortion-corrected dataset [38]. The unit-less FA is an anisotropy index and ranges from 0 in fully isotropic diffusion to 1 in fully anisotropic diffusion [39]. Mean FA will be calculated for the affected and unaffected sides of each patient within a 5-mm radius of the posterior limb of the internal capsule. For methods, see Radlinska et al. [40]. Based on this, the diffusion indicators of rFA and FAasy are calculated for both participant groups using the following formula:$$\begin{array}{l}rFA=\frac{F{A}_{ipsilesional}}{F{A}_{contralesional}}\\ F{A}_{asy}=\frac{F{A}_{contralesional}-F{A}_{ipsilesional}}{F{A}_{contralesional}+F{A}_{ipsilesional}}\end{array}$$

The values of rFA and FAasy ranged from 0 to 1. The lower the rFA and the higher the FAasy, the more significant the decrease in ipsilateral CST anisotropy of the lesion, i.e., the more severe the impairment of CST integrity.

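### Grouping patients by FA quartile after enrolment cannot balance or standardise corticospinal tract integrity, and the outer groups hold only about 6 patients per arm

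*Protocol article*

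**What the plan says.** The abstract (Background and purpose) offers a reason for earlier negative trials: "Considering that previous studies did not stratify patients based on structural retention". The Introduction builds on this. It treats baseline assessment of the corticospinal tract (CST) as necessary for comparable patients, and lists the use of CST integrity among the trial's distinguishing features, as something that limits disturbance of the randomisation. The means it names is an analysis: "Post-enrollment, we will conduct a subgroup analysis to ensure balanced rehabilitation potential across various patient populations".

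Statistical analysis gives the detail. FA is split into three groups (below the 25th percentile, 25th to 75th, above the 75th), a "method post the inclusion of all individuals to standardize the baseline conditions of the patients".

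Randomization and blinding describes a sequence generated in SPSS and concealed in opaque sealed envelopes: "Patients will be assigned randomization numbers based on the order of enrollment". It names no CST or FA stratum and no minimisation factor.

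In Statistical analysis, the repeated-measures ANOVA has time and group as its factors. The FMA-UE regression has treatment, the baseline outcome and a two-level impairment severity. The only interaction named is treatment by impairment severity, and impairment severity is not defined. FA, rFA and FAasy are not named in either model.

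Image data acquisition and preprocessing derives two relative indices of tract damage: "The lower the rFA and the higher the FAasy, the more significant the decrease in ipsilateral CST anisotropy of the lesion". Statistical analysis refers only to FA values.

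**The concern.** The plan claims a property that its design does not have. Balance between arms comes from the allocation; adjustment comes from a term in the model. A subgroup split made once everyone is enrolled supplies neither: each patient stays in the assigned arm, and the overall treatment estimate is the same as if no split had been made.

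This matters because structural preservation is the stated reason why this trial should succeed where others gave conflicting results. Left as it is, the report could say that CST integrity was standardised or balanced when only a split by FA was done. The variable the authors expect to govern recovery would be used only in small groups, and the precision that adjustment for it could bring would be lost.

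**Working it through.** **Inputs.** Sample size estimation: "resulting in the adjusted sample size of *N* = 50, or 25 patients in each group"; "considering significance level (*α*) = 0.05"; power 0.95; d = 1.13 for 9 FMA-UE points; 44 patients before attrition. Study design: 1:1 allocation. Statistical analysis: quartile cut-points. Sidedness is not stated for the sample size; two-sided is used because it reproduces the 44.

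**1. The plan's own figure.** Two-sample t-test, noncentrality d × √(n/2). With n = 22 per arm: 1.13 × √11 = 3.75 on 42 df, critical value 2.018, power 0.956. This gives 22 per arm, 44 in total, as stated. Raising 44 to 50 fits the 10–15% attrition allowance. The calculation is sound and covers the overall comparison only; at 25 v 25 the power is 0.975.

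**2. Size of the FA groups.** Outer groups: 0.25 × 50 = 12.5, so 12 or 13 patients, about 6 per arm. Middle group: about 25 patients, 12 or 13 per arm. If only 44 are evaluable, an outer group has 11.

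**3. Power if an FA group were tested alone at d = 1.13.**

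| Split | Power |
|---|---|
| 6 v 6 | 1.13 × √3 = 1.96 on 10 df, critical value 2.228: 0.425 |
| 4 v 8 | 0.386 |
| 12 v 13 (middle group) | 0.771 |

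At 6 v 6 the effect detectable with 80% power is 1.80 SD. The implied SD is 9 / 1.13 = 7.96, so this is 1.80 × 7.96 ≈ 14.3 FMA-UE points against the planned 9.

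**4. Split of an outer group between arms.** FA is not a described allocation factor, so the split is left to chance. With 25 v 25 overall and 12 patients in the group, the number in one arm is hypergeometric (50, 25, 12). The probability of 8:4 or worse in either direction is 0.321; with 13 patients, the probability that one arm has 4 or fewer is 0.196.

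**5. Chance imbalance in baseline tract integrity.** SE of the standardised mean difference: √(2/25) = 0.283. P(imbalance above 0.4 SD) = 2 × [1 − Φ(0.4/0.283)] = 0.157. The FA split leaves this unchanged.

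**6. Effect modification.** The low-versus-high-FA difference in treatment effect has SE √(4/6.25) = 0.80 SD, so 80% power needs about 2.8 × 0.80 = 2.24 SD. The documents give no modification slope, so a range is assumed. Simulated power at n = 50 (two-sided 5%, residual SD 1, normally distributed rFA; 1-df continuous interaction against a 2-df test over three quartile groups):

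| Assumed change in effect (SD per SD of rFA) | Continuous | Three groups |
|---|---|---|
| 0.3 | 17% | 11% |
| 0.5 | 39% | 24% |
| 0.8 | 73% | 50% |

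A slope of 0.8 means that the effect differs by 1.6 SD (1.6 × 7.96 ≈ 12.7 points) between patients 1 SD below and 1 SD above the mean, more than the whole planned effect.

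**The case against.** The strongest reply is that the main analysis is not damaged. Randomisation keeps the group comparison unbiased whether or not FA is balanced, and the 16% in step 5 would hold for any unstratified covariate at 25 v 25. The regression also adjusts for baseline FMA-UE, which may absorb part of an imbalance in tract integrity. The sample size claims no power for subgroups. All of this stands.

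Four stronger readings are tempting, and the text does not support them.

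- A reader might infer that the plan will report separate p-values within each FA quartile. It does not say how the FA groups will be tested. The power figures in step 3 show what such tests could do; they do not describe a planned analysis.
- A reader might infer that effect modification is not formally tested. A two-sided 5% interaction test is planned, but for impairment severity.
- A reader might infer that FA is certainly absent from every model. Impairment severity is undefined, and its sentence follows shortly after the FA sentences, so it could be meant to reflect tract damage. Two levels do not match three FA groups, and no link is stated. What can be said is that FA is not named as a term.
- A reader might infer that a continuous interaction would make the trial adequate for this question. Step 6 shows that it would not, unless the modification is large.

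The mention of FA rather than rFA may be shorthand in a condensed article. It needs reconciling but is a minor matter.

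**Conclusion.** The statements that FA subgrouping balances or standardises patients are wrong as written, and no further detail in an unseen analysis plan could make them right. The stratification rationale is not carried into the described randomisation or into a named model term. The outer groups, about 6 per arm with 42% power at d = 1.13 if tested alone, can support exploratory description only.

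The documents do not support calling the main comparison biased or invalid: the cost there is precision. Group sizes and chance splits rest on 50 patients with usable DTI and simple 25 v 25 allocation. The interaction powers rest on assumed slopes and are given as a range for that reason.

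**What to change.** 1. Delete the statements in the Introduction and Statistical analysis that subgrouping balances or standardises patients.
2. Add baseline rFA, as defined under Image data acquisition and preprocessing, as a continuous covariate in the FMA-UE regression.
3. Assess effect modification by one treatment-by-continuous-rFA interaction, labelled exploratory because its power is low unless the modification is large.
4. Show results by FA group descriptively, with estimates and intervals.
5. Reconcile the FA values in Statistical analysis with rFA and FAasy, and define impairment severity, saying whether it refers to tract damage.

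The cost is one or two model degrees of freedom and a rule, set in advance, for patients whose DTI is unusable. DTI is already a planned evaluation, so no new data are needed. Stratifying the randomisation on a fixed rFA cut is optional, and possible only if the baseline DTI is read before allocation, which the article does not say.
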